### Statistical Analysis Overview

The primary analysis will follow an intention-to-treat approach, with supportive per-protocol analysis excluding major deviations (eg, early crossovers or missing postbaseline ABG values) and a safety set analyzed as treated. The main end point, percentage change in PaCO_2_ at 60 minutes, will be assessed using analysis of covariance (ANCOVA) adjusting for baseline PaCO_2_ and prespecified covariates (eg, etiology, baseline pH, and age). Noninferiority will be concluded if the upper bound of the 2-sided 95% CI for the HVNI–NIPPV adjusted difference is below the 4.3% margin. A prespecified sensitivity analysis will repeat the primary ANCOVA model using absolute change in PaCO_2_ at 60 minutes as the dependent variable to assess whether the conclusions are robust to the choice of relative vs absolute outcome metric. Secondary endpoints (percentage PaCO_2_ changes at 30 minutes, respiratory rate, and modified Borg Dyspnea Scale) will use similar adjusted models, whereas binary outcomes (treatment failure, intubation, and adverse events) will be compared using chi-square or Fisher exact tests and logistic regression, and length of stay and mortality will be assessed via nonparametric or time-to-event and logistic methods. Missing data handling will focus primarily on the primary outcome (percentage change in PaCO_2_ at 60 minutes). Missing 60-minute ABG results may occur due to early treatment crossover, intubation before the 60-minute time point, patient refusal of repeat ABG, or technical failure of the ABG analyzer. Multiple imputation by chained equations will be performed, with the imputation model including baseline PaCO_2_, baseline pH, treatment arm, age, etiology, respiratory rate, and 30-minute PaCO_2_ (if available). A minimum of 20 imputed datasets will be generated, and results will be pooled using the Rubin rules.

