Sensitivity analyses will include (1) complete-case analysis (excluding participants with missing primary outcome data) and (2) worst-case imputation for the HVNI arm (assigning the worst observed percentage change to missing values in the HVNI arm and the best observed percentage change to missing values in the NIPPV arm), which is a conservative approach for noninferiority trials. Baseline covariates with missing data (expected to be minimal) will be handled through multiple imputation within the same multiple imputation by chained equations framework. Missing secondary outcomes will be analyzed using available data, with the extent of missingness reported for each outcome. Secondary endpoints will be treated as exploratory without formal multiplicity adjustment.

Prespecified exploratory subgroup analyses will be conducted to assess potential heterogeneity of treatment effect. Subgroups will include (1) COPD vs non-COPD etiology, (2) baseline PaCO_2_ strata (eg, 45‐60 mm Hg vs >60 mm Hg), and (3) baseline pH strata (eg, 7.25‐7.35 vs <7.25). Subgroup effects will be evaluated by including interaction terms (subgroup × treatment) in the primary ANCOVA model. These analyses are exploratory and hypothesis generating; the trial is not powered for subgroup comparisons, and results will be interpreted with caution.

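### Borg score, respiratory rate and, less so, 30-minute PaCO2 are analysed on available data only, so patients unmeasured after early intubation or deterioration drop out of these exploratory comparisons

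*Protocol article*

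**What the plan says.** All of this is in the Statistical Analysis Overview of the protocol article unless stated otherwise.

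- The missing-data plan centres on one endpoint: "Missing data handling will focus primarily on the primary outcome (percentage change in PaCO_2_ at 60 minutes". That endpoint gets multiple imputation by chained equations, a complete-case analysis and a worst-case analysis set against HVNI.
- The predictors in the imputation model include "respiratory rate, and 30-minute PaCO_2_ (if available".
- The plan expects loss connected with the patient's course: "Missing 60-minute ABG results may occur due to early treatment crossover, intubation before the 60-minute time point, patient refusal of repeat ABG".
- For the other endpoints the rule is "Missing secondary outcomes will be analyzed using available data, with the extent of missingness reported for each outcome". The plan also declares these endpoints exploratory, with no adjustment for multiplicity.
- The continuous bedside measures (30-minute PaCO2, respiratory rate, Borg) are to be modelled with covariate adjustment in the manner of the primary outcome. The outcomes that count failed patients as events are handled apart: "binary outcomes (treatment failure, intubation, and adverse events) will be compared using chi-square or Fisher exact tests and logistic regression".
- The last paragraph of the Discussion says the primary endpoint will be interpreted jointly with the prespecified secondary outcomes and sensitivity analyses.

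**The concern.** A patient who is intubated before an assessment cannot report a Borg score. The respiratory rate at that time is either not recorded or set by the ventilator, and the plan does not say which value, if any, is analysed. Loss of responsiveness has the same effect on Borg. An available-data analysis then compares the patients who remained measurable, who on average are likely to be doing better. If one arm loses more patients this way, its mean improves for that reason alone.

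Unequal loss is plausible in an open-label trial. The Discussion itself concedes that lack of blinding may affect escalation decisions and subjective measures.

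The primary outcome is protected against this by imputation and a worst-case check. The bedside secondary outcomes have no stated check of either kind. Reporting how much is missing describes the loss but does not show what it does to the comparison. What is at stake is the supporting evidence on dyspnoea, respiratory rate and early gas exchange, not the noninferiority test.

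**Working it through.** **1. The plan's own figure.** The article gives no number for missing secondary outcomes. Its only related figure is the sample size, which reproduces: per arm, 2 × (1.96 + 0.8416)² × 6.65² / 4.3² = 37.5, so 38; 76 in total; 76 × 1.10 = 83.6, so 84. The 10% allowance is for the primary endpoint only. This does not bear on the point.

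**2. Which secondary outcomes are exposed.** I traced each to how it is captured (Rescue, Failure, and Crossover Criteria; Outcome Measures; Statistical Analysis Overview).

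| Outcome | Value after early intubation or deterioration | Exposed? |
|---|---|---|
| Borg at 30 and 60 min | Self-report not obtainable once intubated or unresponsive | Yes |
| Respiratory rate at 30 and 60 min | Missing or ventilator-driven | Yes |
| % change in PaCO2 at 30 min | Lost only if the gas is not drawn by 30 min | Less |
| Treatment failure, conversion, ED intubation | Patient counts as an event; all crossovers and intubations are recorded | No |
| Adverse events | Not tied to completing 60 min on the device | No |
| ICU and hospital stay, inpatient mortality | Taken from the health record after discharge | No |

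The 30-minute gas is less exposed because the stated causes of loss concern the 60-minute gas, some failure criteria are themselves assessed at or after 30 minutes, and patients needing immediate intubation are excluded. It is not immune: intolerance and impending respiratory failure carry no 30-minute threshold.

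**3. Illustration on the Borg scale.** Every input is assumed: failures would score 7, others 3, and every failure is unmeasured.

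- Failure 15% HVNI, 5% NIPPV: HVNI 0.85 × 3 + 0.15 × 7 = 3.6; NIPPV 0.95 × 3 + 0.05 × 7 = 3.2; difference 0.4.
- Failure 10% and 5%: 0.90 × 3 + 0.10 × 7 = 3.4; 3.4 − 3.2 = 0.2.
- Available data in both cases: 3 − 3 = 0.

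With 42 per arm, 15% and 5% are about 6 and 2 patients (6.3 and 2.1). If only half of the failures in each arm were unmeasured, available data would give (2.55 + 0.525)/0.925 − (2.85 + 0.175)/0.975 = 3.32 − 3.10 = 0.22, so 0.18 of the 0.4 would be hidden. For these rates and scores, 0.4 and 0.2 are therefore upper values.

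**4. Illustration in SD units.** Assume no true difference between arms, and that a fraction f is lost from the worst end of a latent score with correlation r to the outcome. The mean of those kept is −r × φ(z)/(1 − f), where z is the (1 − f) normal quantile. For 15% against 5% and r = 1: −0.2332/0.85 + 0.1031/0.95 = −0.274 + 0.109 = −0.17. A simulation gave the same values. Negative means that the arm losing more patients looks better.

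| Loss | r = 0 | r = 0.5 | r = 1 |
|---|---|---|---|
| 10% vs 10% | 0.00 | 0.00 | 0.00 |
| 15% vs 5% | 0.00 | −0.08 | −0.17 |
| 20% vs 10% | 0.00 | −0.08 | −0.15 |
| 30% vs 10% | 0.00 | −0.15 | −0.30 |

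The bias needs loss that is both related to the outcome and different between arms. With equal loss and like selection, or with unrelated loss, it is zero.

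**The case against.** The case against is substantial, and most of it stands.

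- A reader might infer that the rule removes failed patients from the secondary outcomes in general. It does not: failure, conversion and intubation count them as events and would reveal an excess. The rule also drops missing values, not failures. A patient who crosses over awake and is still measured stays in the analysis.
- A reader might infer that the rule hides inferiority. The documents do not support this. Noninferiority is judged only on 60-minute PaCO2, which has its own imputation and worst-case analysis. The secondary endpoints are declared exploratory, and missingness is to be reported for each.
- A reader might assume that the bias favours HVNI. The Introduction describes intolerance and therapeutic failure on NIPPV, so it could run the other way.
- A reader might think that the existing imputation already covers all three measures. The model names respiratory rate without a time point, takes 30-minute PaCO2 only if available, and does not list Borg. Chained-equations imputation in its standard form also assumes that loss depends on observed data. Imputing a spontaneous rate for an intubated patient would be hard to interpret.
- Making worst-rank Borg the main analysis would change the question to a composite that overlaps the failure and intubation outcomes.

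What remains is that these bedside measures have a fixed rule which can omit the sickest patients, no check on it, and a declared role in interpreting the primary result.

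**Conclusion.** The point holds for Borg and respiratory rate at 30 and 60 minutes and, more weakly, for 30-minute PaCO2. It is a minor improvement to exploratory analyses. It does not affect the other secondary outcomes, the sample size or the noninferiority decision.

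The size cannot be known from the documents, which give no failure or loss rates by arm. On the assumed rates above, the distortion is 0.2 to 0.4 Borg points at most, or between zero and 0.30 SD. The direction depends on which arm loses more patients. The conclusion rests on early intubation or deterioration being a real cause of missing bedside values. The article says so for the 60-minute gas; for Borg and respiratory rate it is an inference from what can be measured in an intubated patient.

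**What to change.** 1. Analyse percentage change in PaCO2 at 30 minutes on the imputed datasets generated for the primary outcome, stating that the 30-minute value is itself imputed where missing.
2. Keep the available-data analysis of Borg and respiratory rate. Add a prespecified sensitivity analysis that gives the worst rank to patients with no value because of intubation or deterioration and compares the arms by a rank method. State how a rate recorded during mechanical ventilation is treated.
3. Report these outcomes beside the failure and intubation rates by arm, so that the reader can see who is missing.

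The cost is a little more analysis work, and the worst-rank result is a composite rather than a pure symptom score, which is why it belongs in a sensitivity analysis. It needs the reason for each missing bedside value; crossovers and intubations are already recorded with their time and cause. No additional patients are needed. With 19 of 84 enrolled as of July 2026 and analysis planned only after enrolment ends, there is time to prespecify it.

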### Randomization and Allocation Concealment

Enrollment will be through convenience sampling of eligible ED patients triaged as “urgent” or “immediate.” All study investigators are full-time clinicians with an average of 16 to 20 shifts per month to cover as many shifts as possible for enrollment. Participants will be randomized 1:1 to HVNI or NIPPV using variable block sizes generated by an independent web-based platform [22]. The specific block sizes are not disclosed in this manuscript to prevent prediction of the allocation sequence. Allocation will be implemented via sealed, opaque, sequentially numbered envelopes, with allocation concealment maintained until randomization is completed.

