### Sample Size

A total of 84 patients (42 per group) will be enrolled to provide 80% power and one-sided α of 2.5% to demonstrate noninferiority [25] assuming an SD of 6.65% for percentage change in PaCO_2_ levels before and after treatment [26] and a noninferiority margin of 4.3%. The sample size includes an estimated 10% allowance for missing primary end point data. The noninferiority margin of a 4.3% absolute difference in percentage change was informed by clinician judgment (number of specialist accredited [board-certified] emergency physicians, n=14) of clinically acceptable differences and literature on PaCO_2_ responses to NIPPV. For example, emergency physicians opined that a change from 70 mm Hg to 63 mm Hg using HVNI (−10.0%) was considered noninferior to a change in PaCO_2_ from 70 mm Hg to 60 mm Hg after treatment with NIPPV (−14.3%).

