Using early change in PaCO_2_ as the primary outcome represents both a strength and a limitation. PaCO_2_ directly reflects alveolar ventilation and offers an objective, timely measure of ventilatory response. However, it is a surrogate that may not fully capture longer-term clinical effectiveness, and its relationship to ventilation is nonlinear across baseline values; equivalent absolute changes can imply different physiological effects at different baseline PaCO_2_ levels [30]. Early reductions may overestimate clinical benefit in some patients, particularly those presenting with severe hypercapnia and very high baseline PaCO_2_ levels. Accordingly, interpretation of the primary end point will be integrated with prespecified secondary outcomes and sensitivity analyses. If noninferiority is established with acceptable safety and tolerance, subsequent clinical trials focused on patient-centered and longer-term outcomes, including cost-effectiveness and broader implementation, would be warranted.

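### Effect modification by baseline PaCO2 and pH is tested on two-level strata; exploratory tests on the continuous values would use more of the information (minor, cheap improvement)

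*Protocol article*

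**What the plan says.** In the protocol article, the Statistical Analysis Overview sets out the exploratory subgroups: "Subgroups will include (1) COPD vs non-COPD etiology, (2) baseline PaCO_2_ strata", followed by baseline pH strata. The PaCO2 and pH strata each have two levels, with 60 mm Hg and 7.25 given as example cuts. Heterogeneity is to be assessed by adding subgroup × treatment interactions to the primary ANCOVA. The same section describes that ANCOVA as "adjusting for baseline PaCO_2_ and prespecified covariates (eg, etiology, baseline pH, and age" and similar. Baseline PaCO2 is therefore a definite covariate, and pH is one of the examples. No interaction of treatment with continuous PaCO2 or pH is mentioned. The section labels the subgroup analyses exploratory and says that the trial is not powered for them.

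**The concern.** Cutting a continuous modifier in two treats every patient within a stratum as alike. With a cut at 60 mm Hg, a patient at 61 and a patient at 95 contribute identically to the interaction. If the treatment difference changes steadily with baseline PaCO2 or pH, the split discards part of the evidence for that change. The sample is small: after the planned 10% allowance for missing endpoints, about 76 of 84 patients would be evaluable. Interaction tests are weak at that size, so a further avoidable loss makes an exploratory result harder to read. What is at stake is how informative these secondary analyses are, not the main result.

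**Working it through.** **Inputs from the protocol article.** Sample Size section: "A total of 84 patients (42 per group) will be enrolled to provide 80% power and one-sided α of 2.5% to demonstrate noninferiority", "assuming an SD of 6.65% for percentage change in PaCO_2_ levels before and after treatment", "a noninferiority margin of 4.3" percentage points, and "The sample size includes an estimated 10% allowance for missing primary end point data". Eligibility Criteria: PaCO2 above 45 mm Hg and pH below 7.35, which truncates both modifiers. No mean, SD or share above 60 mm Hg is given for baseline PaCO2, and none for pH, so every distribution below is an assumption.

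**The plan's own figure.** n per arm = 2 × [SD × (z0.975 + z0.80) / margin]² = 2 × [6.65 × (1.960 + 0.842) / 4.3]² = 37.54. Dividing by 0.9 gives 41.7, so 42 per arm and 84 in total. The stated size reproduces. Evaluable patients: 84 × 0.9 = 75.6, about 76. The document gives no figure for the subgroup tests.

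**Information kept by a split.** For a linear modifier effect, this is the squared correlation between the modifier and its two-level version. For a normal modifier with a share p on one side of the cut, it equals φ(z_p)² / [p(1 − p)].

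| Split (normal modifier) | Kept | Lost |
|---|---|---|
| 50/50 | 2/π = 0.637 | 36% |
| 40/60 | 0.622 | 38% |
| 30/70 | 0.576 | 42% |
| 20/80 | 0.490 | 51% |

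At a median split, 76 patients are worth about 76 × 0.637 = 48 patients analysed continuously.

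**Assumed distributions respecting the eligibility limits.**

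- PaCO2 cut at 60, near-normal shape, mean about 59–62 mm Hg: 33–36% lost.
- PaCO2 cut at 60, mean about 68–73 mm Hg or right-skewed: about 45–60% lost in most cases.
- PaCO2 cut at 60, right-skewed with mean near 78 mm Hg: about 68% lost.
- pH cut at 7.25, bell-shaped or skewed: about 33–43% lost.
- Most favourable case tried for either variable (uniform, cut at its middle): 25% lost.

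The worked example in the Sample Size section starts at 70 mm Hg. If typical baselines lie near that value, a cut at 60 is off-centre and the loss is nearer a half than a third.

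**Power of the interaction test.** Simulation of 76 patients, 1:1 allocation, residual SD 6.65, two-sided 5%, continuous baseline kept as a main effect in both models. Baseline PaCO2 is assumed normal with mean 65 and SD 14, cut at 60. The slope is the change in treatment difference, in percentage points, per mm Hg.

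| True slope | Shift from 50 to 80 mm Hg | Continuous | Split |
|---|---|---|---|
| 0.3 | 9 points | 73% | 52% |
| 0.2 | 6 points | 42% | 27% |
| 0.1 | 3 points | 15% | 10% |

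Type I error was about 5% for both. Truncating at 45 mm Hg lowers all the figures (62% vs 39%, 33% vs 20% and 12% vs 8%) but leaves the ordering unchanged. Absolute levels move by a few points between simulation runs and settings.

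**The case against.** The strongest reply is that this is a preference about analyses which the plan already calls exploratory and unpowered, so nothing is stated wrongly and no main conclusion depends on it. That sets the weight at minor. It does not give a reason to discard information, because low power argues for the more efficient test.

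The cuts are only examples, and so is pH as a covariate. That is correct, and it means that the plan cannot be said to fix 60 mm Hg or 7.25. The two-level form of the test is nevertheless stated.

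The larger simulated slopes are big: a 9-point shift between 50 and 80 mm Hg is more than twice the 4.3-point margin. At a 3-point shift neither version is informative. This stands, so the gain in power is material only if heterogeneity is substantial.

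A continuous test assumes a functional form, and a true step at the cut would favour the split. This also stands, which is why the change needs a nonlinearity check.

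Two stronger readings are tempting. A reader might infer from the Discussion's remark that "equivalent absolute changes can imply different physiological effects at different baseline PaCO_2_ levels" that the authors themselves expect the HVNI–NIPPV difference to vary gradually with baseline. The remark concerns how to interpret a given PaCO2 change; it predicts nothing about the difference between arms. A reader might also think that the split undermines the relative-versus-absolute question. The protocol handles that question with its prespecified ANCOVA on absolute change, not with the strata.

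**Conclusion.** The point holds as a minor, inexpensive improvement. For an effect that is roughly linear in the modifier, two-level strata lose about 36% of the information at a median cut of a normal variable, and about 25% to 68% across the distributions tried. None of these figures comes from the documents, which give no baseline distribution, so about a third should not be quoted as a property of this trial. With a true step at the chosen cut the loss would be nil. COPD versus non-COPD is binary by nature and is not touched. The noninferiority conclusion does not depend on any of this, and a reader should not infer that it is weakened.

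**What to change.** Make treatment × continuous baseline PaCO2 and treatment × continuous baseline pH the exploratory interaction tests in the ANCOVA, with a check for nonlinearity. Report the adjusted HVNI–NIPPV difference with its 95% CI across the range of baseline values where there are enough patients. Keep the PaCO2 and pH strata for display only, with cut-points fixed before the data are seen. Leave the COPD subgroup as it is.

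The cost is a few lines of model wording. No extra data or patients are needed, and the protocol article reports 19 of 84 enrolled, with analysis to start only after enrolment ends. The downside is that a functional form has to be assumed and that estimates at extreme baseline values will be imprecise.

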### Data Collection and Management

Data will be recorded on paper-based standardized CRFs using trial numbers only and will be stored under lock and key with restricted access. Electronic data will be stored on secure, access-controlled systems with password protection and audit trails. The ABG samples will be analyzed at the bedside using the i-STAT Alinity analyzer. The analyzer generates a printed result slip that includes PaCO_2_, PaO_2_, pH, bicarbonate, and other parameters with a time stamp. The printed result slip will be attached to the paper-based CRF for each participant. Should the printed result slip be unavailable, illegible, or degraded over time, the ABG results will be retrieved electronically from the analyzer and from the patient’s EHR. Study investigators will transcribe key ABG values onto the CRF in real time. Device settings (flow rate, FiO_2_, and temperature for HVNI and IPAP, EPAP, and FiO_2_ for NIPPV) will also be recorded on the CRF at baseline, 30 minutes, and 60 minutes. Accordingly, the study CRF serves as the primary source document to ensure complete and accurate capture of primary outcome data.

Apart from ABG readings, other variables and outcomes as stated will be collected and followed up on through electronic medical record review. To ensure data accuracy, the following quality checks are in place: (1) double data entry by 2 independent data entry staff members, with discrepancy resolution; (2) programmed range and logic checks during electronic data entry; (3) periodic source data verification by the study coordinator comparing CRF entries against ABG printouts and EHR records; and (4) audit trails for all electronic data modifications.

